## Abstract

Early childhood education aims to achieve the motor, cognitive, emotional, and social development of preschoolers by providing them with a variety of learning opportunities. The square-stepping exercise (SSE) is a balance and lower limb strength training programme used to prevent falls and stimulate cognitive function in older adults. This project aims to propose an SSE tele-exercise (Tele-SSE) protocol to evaluate its effects on the motor and cognitive development of children aged between 3 and 6 years. A randomized controlled trial with experimental (Tele-SSE) and control (general education) groups will be carried out. The application of Tele-SSE will be performed for 9 months (three times per week) and one additional follow-up after the intervention at the beginning of the next academic year. One-hundred and two preschoolers will be recruited and randomly distributed into the two groups: experimental (*n* = 51) and control (*n* = 51). Although the main outcome will be balance due to the nature of the SSE, outcomes will include physical and motor (body mass index, waist circumference, handgrip and lower-limb strength, speed-agility, and cardiorespiratory fitness) and cognitive (executive functions and attention, episodic memory, and language assessment, using the Fitness Assessment in the Preschool Battery (PREFIT) and The National Institutes of Health Toolbox—Early Childhood Cognition Battery. This project aims to improve cognitive and motor skills in preschoolers aged between 3 and 6 years old, based on a 9-month Tele-SSE intervention. If this intervention proves to be effective, it could be implemented in those centres, entities and associations specializing in early childhood education.

## 1. Introduction

Enabling children to achieve their full developmental potential is one of the main objectives to be covered by teachers through educational action. The Spanish Early Childhood Education Curriculum states that all educational actions will aim to contribute to the physical, affective, social, and intellectual development of children. Furthermore, this document adds that attention must be paid to achieve properly affective development, movement and body control habits, communication and language, coexistence of elementary patterns and social relations, as well as to the discovery of environmental physical and social characteristics, focusing on sensory education [1].

Likewise, this document also indicates that the second cycle of childhood education (from 3 to 5−6 years old) will contribute to the development of children’s capacities that will allow them to know their own and other children’s bodies, acquire coordination and general dynamic control, act safely, and learn to value and respect personal differences. Thus, the development of activities that encourage peer-to-peer partnership and movement skills will contribute to achieving these objectives [1].

Gross motor skill activities, such as balancing, crawling, walking, running, cutting and jumping are developed during early childhood and are considered essential elements of motor development [2]. Thus, it seems important to provide preschool children with motor opportunities that favor their motor and cognitive development. Executive functions are a set of cognitive skills necessary for goal-oriented behavior. There is some agreement on considering inhibition and interference control, working memory, and cognitive flexibility as core sub-processes. From core Executive function, higher-order Executive function are built, including planning (choosing steps to reach a goal), reasoning, and problem-solving. Specifically for TeleSSE, all these processes are needed to planification, execution and adjustment of the different motor patterns of SSE [3].

One tool that could contribute greatly to the development of the aforementioned skills is the educational psychomotor intervention, aimed at children between 0 and 8 years old [4]. It could be useful to help the children to develop their motor, personal and social skills which allow them to adapt to different situations in the preschool setting [5]. Many scientific studies support the importance of psychomotor development and providing opportunities to explore the physical environment, manipulate objects and interact with peers in the first years of life, which will ensure a correct impact on their psychomotor development and their interaction with the outside world [6]. Children with greater psychomotor skills and, therefore, greater success in performing physical and psychomotor activities have more social success and popularity among their peers [7]. Furthermore, a relationship has been shown between the opportunities for motor actions available to children during childhood and their physical competence later in life [8]. Several authors also argue that educational psychomotor intervention contributes to the development of motor and personal competences, as well as social and academic skills [5,9]. Specifically, Ruiz-Esteban et al. [10] analyzed the effectiveness of a motor intervention programme on gross motor skills in preschoolers, reporting statistically significant improvements in the development of fundamental motor skills such as leg and arm coordination. Thus, educational psychomotor intervention could be a powerful tool that allows children to better understand their body image, improve their self-concept, learn to communicate, express their ideas and feelings and develop values such as empathy, respect and collaboration, among others [9]. Therefore, there is no doubt that there is a close relationship between educational psychomotor intervention and preschool children’s motor skills [2]. Thus, psychomotor practices and interventions on movement skills that can improve fitness should be considered during the early school years and at the preschool stage [11].

Motor abilities have been widely studied. The relationship between working on motor skills through physical activity has been found in longitudinal studies [12,13,14,15,16,17] and benefits different parameters, such as cardiorespiratory fitness and general health in children [18,19]. One of the methods that has recently been studied is the inclusion of exergaming as a means of physical activity in children [20]. A recent systematic review by McDonough et al. [21] showed the efficacy of using physical activity on motor skill acquisition, also reporting beneficial effects of physical activity promotion. This review also demonstrated that exergaming-based intervention programmes showed a similar relationship to other traditional programmes.

Focusing on exergaming, several studies have shown the benefits on different populations, such as obese children and adolescents [22], autism spectrum disorder [23], cognitive impairment or dementia [24], and even as a means for mitigating fatigue and the negative effects of confinement and quarantine during pandemic situations such as that caused by COVID-19 [25].

A popular modality of exergaming is the square-stepping exercise (SSE), which is an educational psychomotor intervention activity with a playful and innovative character for the development of motor and cognitive skills in preschoolers. It requires both physical and cognitive effort, specifically attention, memory and executive function [26,27]. The SSE consists of the execution of movement patterns including forward, backward, lateral and oblique steps; the complexity of which increases progressively [26]. However, new pattern proposals can be created that include hand steps, jumps, colours, or flexible surfaces, among others, to stimulate children’s gross motor and cognitive skills.

SSE has shown benefits in functionality, balance, lower limb strength, flexibility and agility, concentration, memory, mental acuity and visual memory in older adults [28,29,30]; as well as in preventing and reducing the number of falls, improving cognitive abilities [31]. Additionally, it has been shown to be effective in pathologies such as multiple sclerosis [32] or type 2 diabetes mellitus [33]. However, there is only one study that has analyzed the effects of SSE in preschoolers, showing cognitive and motor benefits in a small sample [34].

Therefore, this project aims to analyze the effects of a 9-month Tele-SSE programme on the motor and cognitive skills in preschool children. More specifically, the present project evaluates the effects of the Tele-SSE-based programme on static balance, physical fitness, body composition, strength, speed-agility, executive function and attention, processing speed, episodic and working memory and language use in preschoolers. In addition, it aims to promote cooperative work among children to foster social skills and interpersonal relationships.

## 2. Material and Methods

### 2.1. Study Design

Due to the nature of the study, the Consolidated Standards of Reporting Trials Statement (CONSORT) methodology [35] will be followed. A randomized controlled trial with a 1 to 1 assignment ratio to experimental and control groups, respectively, will be conducted.

### 2.2. Ethical Approval

The study has been approved by the Bioethics and Biosafety Committee at the University of Extremadura (approval number: 95/2021). The study has been registered in the Clinical Trials Registry provided by the Australian New Zealand Clinical Trial Registry (Request number: 382451; https://www.anzctr.org.au/, accessed on 5 July 2021).

### 2.3. Sample Size

Sample size computations were calculated based on normative values from the Fitness Assessment in the Preschool Battery (PREFIT) for children aged three years old (most heterogeneous population into the selected age range), specifically data from the one-leg balance test [36], because it will be the primary outcome in this study. Thus, accepting a 0.05 alpha risk and a 0.2 beta risk in a bilateral contrast and assuming a common standard deviation of 5.025 and a correlation coefficient of 0.7 between baseline and final measurement [37]; a total of 102 participants (51 subjects in the experimental group and 51 in the control group) are required to detect a difference equal to or greater than 2.43 units. A loss-to-follow-up rate of 20% has been considered.

### 2.4. Randomization and Blinding

Participants will be randomly assigned to experimental (Tele-SSE) or control groups. Research Randomizer computer software (Version 4.0, Geoffrey C. Urbaniak and Scott Plous, Middletown, CT, USA) (http://www.randomizer.org, accessed on 11 June 2021) [38] will be used to create a simple computer-generated randomization sequence before participants are enrolled (1:1). This process will be performed by a research team member without clinical active participation in the trial. The assignment will be hidden in a password-protected computer file. Although participants will know their group assignment, outcome evaluators and data analysts will be blinded to the assignment.

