### 2.5. Participants

To be included in the study, participants will have to meet the following eligibility criteria: (a) be children aged between 3 and 6 years old; (b) be enrolled in a public early childhood education centre in the autonomous community of Extremadura; (c) complete and sign the informed consent form by their parents or legal guardians; (d) the children’s consent and voluntariness to participate in the intervention be given; and (e) not be suffering any condition or inconvenience that prevents the normal practice of physical activity.

Furthermore, only participants who complete all evaluations (baseline, quarterly interim, final and follow-up) will be considered for analysis. Likewise, experimental group subjects will need to be involved in at least 80% of the classes. Moreover, it will be necessary to obtain consent and approval by the school council, as well as by the teacher/tutor, to carry out the intervention throughout the school year.

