### 2.8. Statistics

Statistical procedures and analysis will be conducted using the Statistical Package for Social Sciences (SPSS, Version 25, IBM SPSS, Armonk, NY, USA) software. Personal data will be kept anonymous.

Kolmogorov−Smirnov and Levene’s test will be used to check the normality and homogeneity of data, respectively. Descriptive data will be expressed as mean and standard deviation (parametric variables) or median and interquartile range (nonparametric variables). Then, independent sample T-test (parametric variables) or Mann−Whitney U-test (nonparametric variables) would be performed to determine whether experimental and control groups are comparable at baseline in terms of participant characteristics. Likewise, to detect whether the cognitive and motor intervention consisting of a one-course (9 months) Tele-SSE program has a statistically significant effect on the motor and cognitive skills of preschoolers, an ANCOVA will be conducted using baseline of the main variable as covariate. Alpha level will be set at *p* ≤ 0.05. The magnitude of differences will be evaluated by Cohen’s d effect size. The effect size thresholds will be interpreted as follows: <0.2, small; 0.2 to <0.8, moderate; ≥0.8, large [47].

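### Simple unstratified allocation and an ANCOVA on baseline alone leave age, over a 3-to-6-year range, to chance in the design and unused in the analysis: a modest, cheaply avoided loss of precision.

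*Protocol article*

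**What the plan says.** Section 2.4 (Randomization and Blinding) says that a program "will be used to create a simple computer-generated randomization sequence before participants are enrolled (1:1"). It mentions no blocking and no stratification factor. Section 2.3 (Sample Size) states that "a total of 102 participants (51 subjects in the experimental group and 51 in the control group) are required", so it expects equal arms.

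Section 2.5 (Participants) requires that participants "be children aged between 3 and 6 years old". Section 2.3 takes its standard deviation from three-year-olds only, on the ground that they are the "most heterogeneous population into the selected age range". Section 2.7 uses different forms of the memory test for the younger and the older children. The document thus treats age as relevant to the outcomes.

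Section 2.8 (Statistics) tests for an effect with an ANCOVA whose only named covariate is the baseline of the main variable. It also provides for t-tests or Mann-Whitney tests that "would be performed to determine whether experimental and control groups are comparable at baseline in terms of participant characteristics". No analysis decision depends on the result of those tests.

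**The concern.** Motor and cognitive scores can be expected to change quickly between 3 and 6 years. When a strong predictor is known for every child before allocation, the usual practice is to balance it by design, adjust for it, or both. This plan does neither.

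Two things are at stake. An unrestricted sequence can give unequal arms and an uneven age mix. The baseline score also captures age only in part, because a single noisy measurement leaves some of the age-related variation in the residual. That variation widens the confidence interval, and a chance age gap can move the estimate. The baseline significance tests do not help, since they neither prevent an imbalance nor correct one.

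**Working it through.** **Inputs from Section 2.3.** Two-sided alpha 0.05 and power 0.80 ("accepting a 0.05 alpha risk and a 0.2 beta risk in a bilateral contrast"); SD 5.025 and correlation 0.7 ("assuming a common standard deviation of 5.025 and a correlation coefficient of 0.7 between baseline and final measurement"); difference 2.43 ("are required to detect a difference equal to or greater than 2.43 units"); 20% loss to follow-up; 51 per arm.

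**Step 1: the plan's own sample size.** The figure reproduces on a change-score variance.
- SD of change = 5.025 × √(2 × (1 − 0.7)) = 3.892.
- n per arm = 2 × (1.960 + 0.842)² × 3.892² / 2.43² = 40.28.
- 40.28 / 0.8 = 50.3, rounded up to 51 per arm, or 102 in total.

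The planned ANCOVA has a smaller residual SD, 5.025 × √(1 − 0.7²) = 3.589. The same formula then gives 34.2 per arm, and 34.2 / 0.8 = 42.8, so 43 per arm or 86 in total. On its own inputs the design has some slack.

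**Step 2: arm sizes, if each child is assigned independently.** The size of one arm is Binomial(102, 0.5), with SD 5.05.
- P(exactly 51/51) = C(102, 51) / 2^102 = 7.9%.
- P(arms differ by 10 or more) = 2 × P(X ≤ 46) = 37%.
- P(41/61 or worse) = 2 × P(X ≤ 41) = 5.9%.

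Power after 20% loss:

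| Split | Change score | ANCOVA |
|---|---|---|
| 51/51 | 80.5% | 86.4% |
| 46/56 | 80.1% | 86.1% |
| 41/61 | 79.0% | 85.1% |
| Average over all splits | 80.1% | 86.1% |

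The average cost is about 0.4 points on the change-score basis and 0.3 on the ANCOVA basis.

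**Step 3: chance age imbalance.** The age distribution is not given, so this step rests on assumptions.
- If one third of the children are three-year-olds, the difference in their share between arms has SE √(2 × (1/3) × (2/3) / 51) = 0.093. P(at least 10 points) = 28%; P(at least 15 points) = 11%.
- If age is uniform over 3 to 6 years (or 3 to 7), the difference in mean age has SE 0.17 (or 0.23) years. P(more than half a year) = 0.4% (or 2.9%).

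**Step 4: precision lost by omitting age, balance outcome.** Assume that the plan's SD and correlation hold within an age group, and that the score rises linearly with age. Let W = 5.025² = 25.25 and B = slope² × Var(age), with Var(age) between 0.67 and 1.0. The slope is an assumption; the document gives none.
- Residual variance with baseline and age: 25.25 × (1 − 0.49) = 12.88.
- Residual variance with baseline only: (B + W) − (B + 0.7W)² / (B + W).

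| Slope (s per year) | Var(age) | B | Residual variance without age | Inflation | Power, 41 per arm |
|---|---|---|---|---|---|
| 1 | 0.67 | 0.67 | 12.94 | 0.5% | 86.4% |
| 3 | 0.67 | 6.03 | 13.32 | 3.4% | 85.4% |
| 3 | 1.0 | 9.0 | 13.47 | 4.6% | 85.0% |
| 10 | 1.0 | 100 | 14.69 | 14.1% | 81.9% |

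With age in the model, power at 41 per arm is 86.6%. However steep the slope, the variance without age cannot exceed 0.6 × 25.25 = 15.15, which is the change-score variance on which the trial was sized.

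**Step 5: a second route.** Suppose age correlates equally with baseline and final score, at 0.3, 0.5 or 0.6, and those two correlate at 0.7. The partial correlation of age with the final score is then 0.13, 0.24 or 0.32. The variance reduction is its square, about 2%, 6% or 10%. If the partial correlation is zero, so is the gain.

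**The case against.** The strongest reply is that nothing here is invalid. Simple randomisation is a legitimate choice, the ANCOVA already adjusts for the baseline score, which carries much of any age difference, and further covariates could be set in an analysis plan that is not shown. Validity is conceded. So is the role of the baseline covariate, which is why the range in Step 4 is modest. The last part stands only partly: the allocation method belongs in the protocol and is stated there, and the section that fixes the ANCOVA names its covariate.

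A reader might infer more than the document supports:

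- **That 51/51 will not be achieved.** The text does not say whether the sequence consists of independent assignments or is a random ordering with fixed totals. The latter would give 51/51 exactly. The 7.9% and 37% apply only to the former, and even then the cost in power is slight.
- **That the arms will be unbalanced on age.** Age is left to chance, with an expected difference of zero at randomisation, and a gap in mean age above half a year is improbable under the assumptions of Step 3.
- **That every outcome loses precision.** Only balance can be modelled from the plan's figures. No correlation with age is given for any outcome, and two forms of one memory test do not show a gain beyond baseline adjustment.
- **That the upper end of the range is a typical value.** The 14% needs a slope of 10 s per year with Var(age) = 1.0, which implies a correlation of 0.89 between age and balance and a pooled baseline-to-final correlation of 0.94, against the planned 0.7.

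The baseline significance tests are a reporting matter; removing them would change no treatment-effect result.

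**Conclusion.** The point holds as an inexpensive improvement to methods that the plan states. Age is known for every child from eligibility, the document itself treats it as relevant, and it enters neither allocation nor the effect model.

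The omission does not bias the randomised comparison, and 102 is not wrong. For balance, leaving age out inflates the adjusted residual variance by about 0.5% to 14% over assumed slopes of 1 to 10 s per year; the second route gives about 2% to 10%. The loss is close to zero if age adds nothing once baseline is known. In the same model, power without age stays at about 82% or more with 41 analysed per arm, so an inference that the trial is underpowered for want of age adjustment is not supported. These sizes depend on the assumed slope, the assumed spread of ages, and a reading of 5.025 and 0.7 as values within an age group.

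**What to change.** In Section 2.4, replace the simple sequence with permuted blocks of varying size, stratified by age or school year. Do not stratify by classroom as well: age bands crossed with classrooms among 102 children would leave many small strata with incomplete blocks, which can bring imbalance back.

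In Section 2.8, prespecify the ANCOVA for each outcome with that outcome's own baseline value, age, and the age stratum used in the randomisation. This also settles whether the baseline of the main variable means each outcome's own baseline or baseline balance, which the abstract calls the main outcome.

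The cost is a slightly more complex list and one or a few model degrees of freedom; age is already recorded. The change to the list must be made before allocation begins, because stratification cannot be added afterwards.

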### 2.5. Participants

To be included in the study, participants will have to meet the following eligibility criteria: (a) be children aged between 3 and 6 years old; (b) be enrolled in a public early childhood education centre in the autonomous community of Extremadura; (c) complete and sign the informed consent form by their parents or legal guardians; (d) the children’s consent and voluntariness to participate in the intervention be given; and (e) not be suffering any condition or inconvenience that prevents the normal practice of physical activity.

Furthermore, only participants who complete all evaluations (baseline, quarterly interim, final and follow-up) will be considered for analysis. Likewise, experimental group subjects will need to be involved in at least 80% of the classes. Moreover, it will be necessary to obtain consent and approval by the school council, as well as by the teacher/tutor, to carry out the intervention throughout the school year.

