#### 2.6.2. Control Group

Participants will continue with their usual school routines and usual classes, carrying out the scheduled activities (handicrafts, cards, free play, etc.) and will only participate in assessments. Thus, they will not take part in Tele-SSE intervention.

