## Figures and Tables

**Table 1 ijerph-18-08649-t001:** Progression of Tele-SSE intervention proposal.

Month	Frequency (Days a Week)	Session Duration (min)	Steps per Sequence (Number)	Difficulty (Level)	Additional Difficulty Variables
1	3	60	2	Beginner 1	
2	3	60	4	Beginner 1 and 2	
3	3	60	4	Beginner 2	
4	3	60	6	Intermediate 1	
5	3	60	6	Intermediate 2	
6	3	60	6	Intermediate 3	
7	3	60	8	Intermediate 3	Colors
8	3	60	8	Advanced 1	Colors
9	3	60	8	Advanced 1	Flexible surface

**Table 2 ijerph-18-08649-t002:** Typical structure of Tele-SSE session.

Typical SSE Session Way
**Warm-up** (10 min)
General
Joint mobility
Stretching
Specific
Cognitive play
Motion game
**Main Part** (40 min)
Review of the patterns learnt in the previous session
Learning and implementation of SSE pattern 1
Learning and implementation of SSE pattern 2
Learning and implementation of SSE pattern 3
Learning and implementation of SSE pattern 4
**Cool-down** (10 min)
Stretching
Relaxation
Final thought
Personal hygiene

**Table 3 ijerph-18-08649-t003:** Assessments schedule for both experimental and control group.

Assessment	Baseline	Month 3	Month 6	Month 9	Beginning of Next Course
BMI	x	x	x	x	x
Waist circumference	x	x	x	x	x
Handgrip strength	x	x	x	x	x
Lower limb strength	x	x	x	x	x
Speed-agility	x	x	x	x	x
Balance	x	x	x	x	x
Cardiorespiratory fitness	x	x	x	x	x
Executive function and attention	x	x	x	x	x
Episodic memory	x	x	x	x	x
Language	x	x	x	x	x

BMI, body mass index; x, measure to be taken on that period of time.

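### The only stated analysis set keeps children who complete all five assessments and, in the Tele-SSE arm alone, appears to require 80% class involvement, so the groups compared are no longer those formed by randomisation

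*Protocol article*

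**What the plan says.** Section 2.1 sets up a parallel-group randomised trial with 1:1 allocation. Section 2.5 lists the eligibility criteria and then defines who is analysed: "only participants who complete all evaluations (baseline, quarterly interim, final and follow-up) will be considered for analysis". The next sentence reads "Likewise, experimental group subjects will need to be involved in at least 80% of the classes". No corresponding condition is set for controls, who under section 2.6.2 "will only participate in assessments".

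Table 3 schedules balance and every other outcome at five times in both groups: baseline, months 3, 6 and 9, and the beginning of the next course.

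Section 2.8 plans an ANCOVA adjusted for baseline to test the effect of the nine-month programme and names no analysis population. No other section overrides section 2.5. The only allowance for losses is in section 2.3: "A loss-to-follow-up rate of 20% has been considered".

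**The concern.** Completing five assessments and attending 80% of classes over nine months are known only after randomisation. Placing these rules beside the eligibility criteria does not make them baseline characteristics.

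- **Completeness rule (both arms).** For the nine-month comparison, the planned ANCOVA needs a baseline score and a month-9 score. A child who has both is still dropped for missing month 3, month 6 or the visit in the next school year. Data that bear directly on the primary outcome are thrown away, and those kept are a selected subset.
- **Attendance rule (Tele-SSE arm only).** Sessions take place in the classroom, so low attendance may reflect school absence, illness or reluctance. Control children may be absent just as often, but they stay in the analysis. One type of child is removed from one arm and kept in the other. Baseline adjustment cannot repair this if attendance relates to outcome beyond the baseline score.

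The same set serves the primary and every secondary outcome. A positive result would be open to the reply that the analysed Tele-SSE children would have done better anyway.

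**Working it through.** **Inputs from the article.** Section 2.3: SD 5.025, baseline-final correlation 0.7, target difference 2.43 (the balance test is recorded in seconds), two-sided alpha 0.05, power 0.80, 20% loss, 51 per arm. Table 3: four post-baseline visits.

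**Assumed, not in the article.** The share of Tele-SSE children below 80% attendance, the correlation c between attendance and baseline-adjusted balance, and the chance of missing a visit.

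**1. The plan's own figure.** SD of change = 5.025 × √(2 × (1 − 0.7)) = 3.892. Per arm, n = 2 × (3.892 × (1.960 + 0.842) / 2.43)² = 40.28. Then 40.28 / 0.8 = 50.35, so 51 per arm and 102 in total. The stated size reproduces. The fault lies in the analysis set, not in the arithmetic.

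**2. Completeness rule.** If each of four visits is missed independently with probability p, the share dropped is 1 − (1 − p)⁴.
- p = 5%: 1 − 0.95⁴ = 19%
- p = 7%: 1 − 0.93⁴ = 25%

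**3. Attendance rule, no true effect.** The ANCOVA residual SD is 5.025 × √(1 − 0.7²) = 3.59 s. Removing the lowest 20% of a normally distributed attendance score raises its mean by φ(z)/0.8 = 0.350 SD. The spurious difference is 0.350 × c × 3.59 s.

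| c | Spurious gain | Share of 2.43 s |
|---|---|---|
| 0 | 0 | 0% |
| 0.1 | 0.13 s | 5% |
| 0.3 | 0.38 s | 16% |

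With 30% removed, the share of the target is 7% to 22% for c from 0.1 to 0.3.

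**4. Check by simulation.** ANCOVA under no true effect, 51 per arm, with only the Tele-SSE arm cut on attendance (20% removed):
- c = 0: mean difference −0.02 s, type I error 0.050
- c = 0.2: 0.26 s, type I error 0.06
- c = 0.3: 0.39 s, type I error 0.08

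These agree with step 3.

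**5. Power.** Take 40.8 per arm after 20% loss (51 × 0.8), then remove a further 20% or 30% of Tele-SSE children for attendance (40.8 × 0.8 = 32.6; 40.8 × 0.7 = 28.6).

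| Tele-SSE vs control | Change score, SD 3.89 | Planned ANCOVA, SD 3.59 |
|---|---|---|
| 40.8 vs 40.8 | 80% | 86% |
| 32.6 vs 40.8 | 75% | 81% |
| 28.6 vs 40.8 | 71% | 78% |

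**The case against.** The strongest reply is that the attendance sentence does not literally say that low attenders are left out of the analysis, and that controls have no Tele-SSE classes to attend, so some asymmetry is built into the design. Both statements are true. But the sentence follows the analysis rule directly and is tied to it by *Likewise*, so exclusion is the natural reading. If something else was meant, the text needs to say so. That controls have no sessions explains why the rule cannot be mirrored; it does not make a one-arm exclusion neutral. The completeness rule is explicit in any case.

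It may also be said that bias is assumed rather than shown. That stands: neither the correlations nor the exclusion rates come from the article. Nor is the direction of any bias from the completeness rule, which applies to both arms, established.

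A reader might infer three stronger points that the documents do not support:

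- **That the stated power is lost.** The shortfall to 75% or 71% arises with the change-score SD. Under the planned ANCOVA, power is 81% with a further 20% removed and 78% with 30%, given the stated correlation of 0.7. The article also does not define what its 20% loss covers, and attendance and visit losses may overlap.
- **That the analysts are necessarily unblinded.** Section 2.4 says "outcome evaluators and data analysts will be blinded to the assignment". A one-arm filter would reveal the arms only if the analysts applied it or saw the attendance records. Someone else could apply it before handing over coded data.
- **That the damage is irreversible.** Table 3 schedules assessments for both groups, and nothing says they stop for low attenders. The data for an as-randomised analysis should therefore exist.

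Finally, this is not a detail left to an unseen analysis plan. The word *only* in section 2.5 fixes the set, and a later plan naming all randomised children would contradict it.

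**Conclusion.** The concern holds as a structural fault in the stated analysis set. One filter discards usable month-9 scores in both arms. The other, on its natural reading, selects on behaviour after randomisation in the Tele-SSE arm only. The plan as written therefore does not deliver a comparison of the groups as randomised.

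The attendance bias is zero if attendance is unrelated to outcome. It favours Tele-SSE if better attenders would have done better anyway, and under the illustrative assumptions it is modest against the target difference. The loss from the completeness rule could take up about the whole 20% allowance at a 5% miss rate per visit and exceed it at 7%, assuming that visits are missed independently. The case for change rests on the selection itself, not on lost power or broken blinding.

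**What to change.** Replace the analysis rule in section 2.5 with wording such as: *The primary analysis includes all randomised children in their assigned group, regardless of attendance, using all available balance data.* Either of two methods would serve:

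- the planned baseline-adjusted ANCOVA on every child with a month-9 score, with a sensitivity analysis for missing data; or
- a baseline-adjusted mixed model over months 3, 6, 9 and follow-up, with the month-9 contrast as primary.

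Keep the set defined by all visits and 80% attendance as a labelled secondary per-protocol analysis. State that children who fall below 80% attendance continue to be assessed on the Table 3 schedule.

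The cost is protocol wording and slightly more analysis work. The sample size stays at 102 and no additional assessments are needed. The downside is that the estimated effect may be somewhat smaller, because low attenders remain in the Tele-SSE arm.
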